## Abstract

**Background:**

Glioblastoma (GBM), the most common glial primary brain tumour, is without exception lethal. Every year approximately 600 patients are diagnosed with this heterogeneous disease in The Netherlands. Despite neurosurgery, chemo -and radiation therapy, these tumours inevitably recur. Currently, there is no gold standard at time of recurrence and treatment options are limited. Unfortunately, the results of dedicated trials with new drugs have been very disappointing. The goal of the project is to obtain the evidence for changing standard of care (SOC) procedures to include whole genome sequencing (WGS) and consequently adapt care guidelines for this specific patient group with very poor prognosis by offering optimal and timely benefit from novel therapies, even in the absence of traditional registration trials for this small volume cancer indication.

**Methods:**

The GLOW study is a prospective diagnostic cohort study executed through collaboration of the Hartwig Medical Foundation (Hartwig, a non-profit organisation) and twelve Dutch centers that perform neurosurgery and/or treat GBM patients. A total of 200 patients with a first recurrence of a glioblastoma will be included. Dual primary endpoint is the percentage of patients who receive targeted therapy based on the WGS report and overall survival. Secondary endpoints include WGS report success rate and number of targeted treatments available based on WGS reports and number of patients starting a treatment in presence of an actionable variant. At recurrence, study participants will undergo SOC neurosurgical resection. Tumour material will then, together with a blood sample, be sent to Hartwig where it will be analysed by WGS. A diagnostic report with therapy guidance, including potential matching off-label drugs and available clinical trials will then be sent back to the treating physician for discussing of the results in molecular tumour boards and targeted treatment decision making.

**Discussion:**

The GLOW study aims to provide the scientific evidence for changing the SOC diagnostics for patients with a recurrent glioblastoma by investigating complete genome diagnostics to maximize treatment options for this patient group.

*Trial registration:* ClinicalTrials.gov Identifier: NCT05186064.

**Supplementary Information:**

The online version contains supplementary material available at 10.1186/s12920-022-01343-4.

## Background

Glioblastoma (GBM), the most common glial primary brain tumour, is almost always lethal. In the Netherlands, every year approximately 600 patients are diagnosed with this heterogeneous disease. Standard treatment for patients with newly diagnosed GBM consists of maximal safe surgical resection followed by postoperative radiation with concomitant and adjuvant temozolomide therapy [1]. Despite this intensive treatment scheme, these tumours inevitably recur and the prognosis of patients remains poor with a median survival of 14 months [2]. At the time of recurrence, only a small number of patients with well-localized tumours are eligible for re-resection. Systemic treatment is commonly suggested for recurrence, of which nitrosoureas or retreatment with temozolomide being mostly used with limited progression-free survival rates at 6 months (15–20%) and objective response rate of less than 10% [3–7]. Patients with an O6-methylguanine DNA methyltransferase (MGMT) promoter-methylated recurrent tumour may benefit from a temozolomide rechallenge, from lomustine or even the combination of both [8–10]. Outside of the European Union, bevacizumab has been approved for relapsed GBM [11, 12]. Some patients with relapsed GBM undergo re-irradiation, which may result in local disease control in a proportion of patients [13–17]. However, this is not always feasible due to the hazards of cumulative (cognitive) neurotoxicity.

Unfortunately, the results of dedicated trials with new drugs have been very disappointing. Target pre-screening, if applicable, was usually performed on archival tumour material, limited gene panels were used and not in every case a central review was performed. Targeted treatment options are becoming increasingly available for cancer patients, however studies on molecular targets for recurrent GBM patients have not yet led to clinical advantages [18]. Still, there is a major unmet need for this patient category as demonstrated by the limited treatment options and very poor survival. Furthermore, the organisation of standard-of-care (SOC) molecular testing for GBM is suboptimal. First, molecular tests are currently performed sequentially, which takes more time, especially in absence of gene panels. Second, because of this organization, tissue might become scarce. Third, different centers use different molecular panels, which are not all tailored towards identifying relevant biomarkers for (experimental) targeted treatments. Whole genome sequencing (WGS) will provide all molecular information in a single test and within a limited time of ten to fourteen days. Furthermore, additional stratification biomarkers for treatments can be identified using WGS. Although WGS is validated as a clinical diagnostic test [19, 20], its implementation in routine care environments is still slowly growing, although in the Netherlands, the non-profit organisation Hartwig provides access to WGS-based testing to all hospitals. The potential of WGS in the area of personalised medicine for patients with cancer has been demonstrated before, but it has never been prospectively studied as a SOC procedure in patients with a recurrent GBM [20, 21].

Actionability of a molecular alteration is based on information in public knowledge bases, including the Clinical Knowledgebase (CKB), Oncology Knowledge Base (OncoKB), the Clinical Interpretation of Variants in Cancer (CIViC), and can be split by evidence levels according to stablished classification levels: including the six level ESCAT classification [22]. Hypothetical target molecular alterations are those that, at minimum, are associated with preclinical evidence linking the alteration with drug activity. According to the ESCAT classification, treatment should then only be considered in the context of early clinical trials and lack of clinical data should be stressed to patients. To demonstrate that such hypothesized treatments are effective, down-stream clinical studies are required which are facilitated by effective and comprehensive identification of these molecular events without repeating past experiences with drugs that were proven to be ineffective. These trials should also investigate and link pharmacodynamics to the clinical utility of the targeted therapy, since not all drugs will effectively cross the blood–brain barrier.

The GLioblastoma targeted treatment Option maximization by Wgs (GLOW) study aims to evaluate the diagnostic value of extensive molecular diagnostics based on complete genome sequencing for patients with a first recurrence of their glioblastoma undergoing surgery for the recurrence. Consequently, this might result in the adaption of care guidelines by offering optimal and timely benefit from novel therapies, even in the absence of traditional registration trials for this small volume cancer indication.

## Objectives

### Primary objective

The primary objective of the GLOW study is to determine the percentage of patients who receive targeted therapy after surgery, including experimental therapy based on the WGS report, which should ultimately result in more effective treatment (not part of the study) and improved survival, which will be measured as overall survival (OS) within GLOW.

### Secondary objectives

There are several secondary objectives in this study. First, improvement of progression-free survival and overall survival by three months for patients that are treated based on WGS results. Second, to determine the percentage of tumour samples with sufficient quality for WGS analysis obtained during routine neurosurgical reresection. Third, to determine the percentage of tumour samples with an informative mutational profile, i.e. the number of patients with actionable mutations and number of actionable mutations per patient. Finally, to determine access to registered drugs for non-registered indications (i.e. off-label use) for these patients in The Netherlands.

## Methods/design

### Study design

The GLOW study is a prospective diagnostic cohort study executed through collaboration of the Hartwig Medical Foundation (Hartwig, a non-profit organisation) and twelve Dutch centers that perform neurosurgery and/or treat GBM patients. The study aims to obtain, besides surgery, a more accurate pre-treatment stratification of recurrent GBM patients by obtaining fresh tumour samples and a blood sample (obtained during reresection as part of SOC) for WGS analysis leading to targeted treatment and eventual better progression free and overall survival. The patient outcomes of the prospective cohort will be compared with a similar-sized multicenter historical cohort of patients, who have not received routine WGS, seen between 2019 and 2020 in Utrecht University Medical Center (UMCU) and Haaglanden Medical Center (HMC). An independent data monitoring committee (DMC) is established to ensure independent trial supervision. The DMC will monitor the recruitment, the reported adverse events and the data quality after inclusion of the tenth patient, and at least once a year. The study design is summarised in Fig. 1. The study is registered on ClinicalTrials.gov with number NCT05186064.

**Fig. 1 Fig1:**
[figure not shown]
Design of the GLOW study with work packages (WP) overview

### Study population

Within two years from the clinical phase, 235 patients will be recruited. Adult patients with a histopathologically confirmed isocitrate dehydrogenase (IDH) wildtype (wt) glioblastoma with a first recurrence after radiotherapy and/or systemic therapy and who are suited for SOC reresection, are eligible to participate in this study. The patients should have a life expectancy of at least three months, allowing adequate follow-up of toxicity and antitumour activity, together with a Karnofsky Performance Status (KPS) of at least seventy, since the patients should be deemed eligible for targeted treatment options, also in a clinical trial setting. Finally, the patients have to be able and willing to give written informed consent. Potential subjects who currently receive antitumour treatment will be excluded, although patients may enter other studies after WGS-based treatment decision making is completed. Patients with any other clinically significant medical condition which, in the opinion of the treating physician, makes it undesirable for the patient to participate in medication studies or which could jeopardize compliance with study requirements including, but not limited to, ongoing or active infection, significant uncontrolled hypertension, or severe psychiatric illness/social situations, will be excluded as well.

### Statistical analysis

There are no formal statistical considerations that underlie this study as the study assesses the impact of using WGS in diagnostics versus current standard of care and patients will receive potentially a broad range of treatments with variable outcome expectations. First interim analysis of the results, on which premature termination or modification of the study will be based, will be started when the clinical follow-up data of 100 WGS analysed patients is available.

### Sample size calculation

The aim is to include a total of 235 patients in this study. Based on clinical expertise, around 15% of the initially included patients are expected to not be able to undergo the planned reresection because of medical conditions or personal choices, resulting in a total of 200 patients who will be included in the GLOW study. Based on previous experience, for about 20% of patients the obtained material is unfortunately not suited for WGS due to insufficient harvest of tumour cells. Collecting procedures aimed for avoiding necrotic and low tumour purity regions and prioritizing the best suited material for molecular diagnostics should minimise this rate. Over the complete project, on average a maximum of 20% of samples will be expected to drop out due to insufficient quality for WGS, mainly due too low tumour purity. This means that a WGS based patient report will be generated for a minimum of 160 patients.

### Sample collection and processing

Study participants will undergo standard reresection of the tumour by the neurosurgeon as part of SOC. The collection of fresh frozen material will be done according to the standard operation protocol. Upon tissue collection, multiple samples will be sent to the pathology department of the neurosurgical center. After confirmation of the diagnosis recurrent glioblastoma, samples including information regarding the tumour cell percentage will be shipped to Hartwig for processing. Although the aim is to use 200 ng of DNA as input for WGS, all tumour samples with a minimum of 50 ng of DNA will be processed. Although not used in this study, RNA will simultaneously be isolated from the same tumour tissue and biobanked for later usage like whole transcriptome sequencing. In addition, a 10 mL blood sample will be collected from the patients to isolate normal germline DNA (i.e., not only from the tumour) in order to be able to discriminate somatic mutations from the patient’s germline DNA background variations. After diagnostic procedures by Hartwig, the samples will be stored in the local biobanks of the corresponding centers.

### DNA sequencing

Only tumours with at least 20% tumour purity will be further processed for deep sequencing by WGS. The tumour purity will be maximised by collecting multiple samples from different regions of the tumour to avoid radionecrotic samples. WGS of the tumour DNA will be performed according to the previously described standard procedures [21]. Samples with the required tumour purity will be deep-sequenced on Illumina Novaseq to an average depth of 90–100 × and the blood control samples to a depth of 30-35x. Thus, a total of four ‘standard 30x’ genome equivalents are generated per patient to be able to filter for abundantly present germline variants and to deal with tumour heterogeneity and presence of non-tumour cells in the tumour sample. This enables the reporting of somatic variants and therapeutically actionable mutations. Hartwig has established procedures for WGS under ISO17025 accreditation and the WGS-based test is already used in routine diagnostics for other indications (e.g. Cancer of Unknown Primary) and in various hospitals in The Netherlands.

### Treatment decision

The WGS report that will be made available by Hartwig (see Additional file 1 for an example) will be sent to the local pathologist and local study coordinator, who will add the report to the electronic patient files and enters relevant information to a nationwide network and registry of histo- and cytopathology in The Netherlands (PALGA) [23]. In addition, patient reports will be returned to the treating medical specialist as well as to central and local principal investigators. The neuro-oncology team will discuss the results and allocate subsequent treatment accordingly. If needed, the local neuro-oncologist can consult a centralized molecular tumour board which will also receive the anonymised report for central data management. In case of a persistent discordance between the results of WGS and SOC diagnostics, the SOC findings will be leading in the treatment decision. Such discrepancies will be followed up with revalidation of the results (e.g. to exclude sample heterogeneity as a cause) including the use of an independent orthogonal assay when needed.

### Ethical considerations

Every patient will be extensively informed about the study goals and (potential) patient impact by a local research nurse, nurse practitioner or clinical specialist, and will have to sign an informed consent before participating in the study. Potential study participants will get one to two weeks, the time between planning surgery and the operation date, to decide on participating and will get the opportunity to ask additional questions or consult the independent expert of the study. Apart from consenting to the collecting, storage and use of their tumour and blood material, the patients will be asked for their consent to being informed about relevant inherited findings in germline DNA and, if so, under which conditions. Participants can limit this choice to disease that are preventable or treatable and can provide their preference for family to obtain access to heritable information after being deceased. This germline consenting model is optimized based on patient preferences [24] and also was applied in the CPCT-02 (open, NCT01855477), WIDE (closed) [25] and DRUP (open, NCT02925234) studies. All adverse events (AEs) reported spontaneously by the subject or observed by the investigator or his staff will be recorded. All AEs will be followed until they have abated, or until a stable situation has been reached. Depending on the event, follow-up may require additional tests or medical procedures as indicated.

### Primary endpoints

Dual primary endpoint is the percentage of patients who receive targeted therapy based on the WGS report and OS. The OS of these patients will be compared to the OS of patients in the historical cohort, who have not had WGS-based treatment, and should be improved by three months at least.

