#### Progression free survival

Finally, data about the median progression free survival after reresection will be collected by calculating the time between the date of the reresection and the date of clinical and/or radiological progression. The aim of the GLOW study is to improve the median progression free survival by at least three months for the patients who are treated based on WGS results compared to patients in the historical cohort who are not treated based on WGS results.

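### PFS, and on the natural reading OS, of WGS-treated patients is set against historical patients from reresection, which favours WGS even with inert drugs; the article also conflicts with itself on the OS analysis set

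*Protocol article*

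**What the plan says.** Four sections of the protocol article describe the outcome comparison.

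- **Primary endpoints.** "Dual primary endpoint is the percentage of patients who receive targeted therapy based on the WGS report and OS". The next sentence reads "The OS of these patients will be compared to the OS of patients in the historical cohort, who have not had WGS-based treatment" and asks for a gain of at least three months.
- **Secondary objectives.** The aim is "improvement of progression-free survival and overall survival by three months for patients that are treated based on WGS results".
- **Progression free survival** (under Secondary endpoints). PFS is obtained by "calculating the time between the date of the reresection and the date of clinical and/or radiological progression". The three-month aim is "for the patients who are treated based on WGS results compared to patients in the historical cohort who are not treated based on WGS results".
- **Study design.** "The patient outcomes of the prospective cohort will be compared with a similar-sized multicenter historical cohort of patients, who have not received routine WGS".

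No time origin is stated for OS. Reresection is the only origin that the article gives for any survival outcome, and both cohorts can share it.

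Sequencing is said in the Background to deliver its result "within a limited time of ten to fourteen days". According to Sample collection and processing and Treatment decision, pathology confirmation and shipping come before it, and discussion by the neuro-oncology team comes after it, with a central tumour board if needed. Targeted treatment options adds access to an off-label drug or a trial.

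**The concern.** Membership of the WGS-treated group is decided by something that happens weeks after reresection. If survival is counted from reresection, treated patients cannot have died in those weeks. For PFS they will in effect also have stayed progression-free. They must also have remained fit enough to start treatment. GLOW patients who died or deteriorated early drop out of the treated group, while their historical counterparts stay in the comparator as early failures. This is immortal time combined with selection for fitness, and both push in the same direction.

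One half of the dual primary endpoint, and the PFS aim, could therefore show an apparent benefit that no drug produced. The article intends the results to support a change in standard diagnostics, and its Discussion ties a significant benefit to cost-effectiveness, so the bias would carry into those conclusions. The conflict over the OS analysis set also leaves open which of two very different contrasts is primary.

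**Working it through.** **1. Size of the treated group, from the article's figures.** The stated flow reproduces: 235 × 0.85 = 199.75 ≈ 200 reresected, and 200 × 0.80 = 160 WGS reports. With at least 75% actionable and 32% of those starting targeted treatment: 160 × 0.75 × 0.32 = 38.4 ≈ 38. If the 32% applies to all reports: 160 × 0.32 = 51.2 ≈ 51. The treated share is thus about 19% (38/200) to 32% (51/160).

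**2. Analysis sets side by side.**

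| Section | GLOW side | Origin |
|---|---|---|
| Progression free survival | WGS-treated only (explicit) | Reresection |
| Secondary objectives (OS and PFS gain) | WGS-treated only (explicit) | Not stated |
| Primary endpoints (OS) | WGS-treated only (natural reading) | Not stated |
| Study design | Whole prospective cohort | Not stated |

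**3. Direction.** With no drug effect, a patient who starts treatment at time s has survival S(t)/S(s) for t > s, which is never below S(t). For exponential survival with median m and a fixed delay s, the treated median is m + s, so the spurious gain equals the delay: m = 9 and s = 2 gives 11 against 9. For a Weibull with shape k and scale λ = m/(ln 2)^(1/k), the treated median is λ[(s/λ)^k + ln 2]^(1/k). With k = 1.3 and s = 2, the gain is 1.03, 0.96 and 0.89 months for m = 7, 9 and 12.

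**4. Size for OS: simulation with no drug effect.** Assumed, not in the documents: 38 treated patients drawn from 120 with an actionable variant, among those alive at a uniformly distributed start time; 200 historical patients; median OS of 7, 9 or 12 months from reresection; exponential or Weibull (1.3) survival; no selection for fitness.

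| Start after reresection | Mean spurious gain in median OS | Chance of an observed gain ≥ 3 months |
|---|---|---|
| Zero delay (noise only) | 0–0.2 month | 2–18% |
| 0.5–1 month | 0.2–1.0 month | 3–24% |
| 1.5–2.5 months | 0.9–2.1 months | 8–37% |
| 1–5 months | 1.7–3.2 months | 17–50% |

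The low end of each mean range is Weibull and the high end exponential. Repeat runs agreed to about 0.1 month and one percentage point. The zero-delay row is the reference for the last column. A landmark at the latest start time in both cohorts cut the mean gain to about 0.3 month or less.

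**5. A second, large-sample simulation.** This used exponential survival and no drug effect. With immortal time alone, mean delays of 0.5, 1, 2 and 3 months gave:
- OS (assumed medians 6–12 months): +0.5, +1.0, about +1.9 and +2.6 to +2.8 months.
- PFS (assumed medians 2–4 months): +0.5, +1.0, +1.6 to +1.8 and +1.9 to +2.4 months. This takes patients as progression-free when treatment starts.

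Adding fairly strong fitness selection (log-hazard SD 0.5; odds of treatment × 0.37 per SD of worse prognosis) gave +2.7 to +7.6 months for OS and +1.3 to +4.4 months for PFS.

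**6. What the whole-cohort contrast would show.** Suppose treatment truly adds 3 months to the median in a fraction f. The whole-cohort median t solves (1 − f)·0.5^(t/m) + f·0.5^(t/(m+3)) = 0.5. For f = 0.19 and m = 6, t = 6.45, a gain of 0.45 month. For f = 0.32 and m = 12, t = 12.86, a gain of 0.86 month.

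**The case against.** The best counter-argument concerns OS. Study design describes a comparison of the prospective cohort with a historical cohort of similar size, which fits 200 patients and not 38. Secondary objectives lists the treated-only OS gain as secondary, so primary OS could be meant as the whole-cohort contrast. This stands as far as it goes: for OS, the article does not settle the analysis set, and the bias is conditional on the treated-only reading. It does not help PFS, where "patients who are treated based on WGS results compared to patients in the historical cohort who are not treated based on WGS results" leaves no whole-cohort reading.

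A reader might also infer three stronger claims that the article does not support.

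- *OS is stated to run from reresection.* Only PFS has that origin in writing. For OS it is an inference, though a start-of-treatment origin does not exist for historical patients who were not treated on WGS.
- *The historical cohort is untreated.* The text says only that it had no WGS-based treatment. The 16% baseline in Targeted treatment options suggests that some historical patients may have had targeted therapy.
- *The whole 8–50% chance of seeing three months is bias.* With zero delay, sampling noise alone gives 2–18%.

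It can also be said that landmark or time-dependent methods belong in a SAP that is not shown, and that Statistical analysis disclaims formal considerations. But the point is not a missing method. The article itself fixes the PFS groups and clock, and a plan that follows it inherits the bias. Having no formal test does not remove a bias in the estimate.

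**Conclusion.** The point holds for PFS as written. For OS it holds on the natural reading of Primary endpoints and the explicit wording of Secondary objectives, subject to the conflict with Study design and an unstated OS origin. The direction follows from the design; the size depends on assumed medians, delays, survival shape and strength of selection.

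It would be tempting to say that immortal time alone delivers the three-month aim with inert drugs. The calculations do not show that in general. The mean spurious OS gain reaches three months only with exponential survival and starts spread over 1–5 months, and in the large-sample runs immortal time alone stayed below three months throughout. It nevertheless uses up a material share of the target once starts fall beyond about 1.5 months, and it raises the chance of an observed three-month gain above the noise level. Selection for fitness would add to it and, if fairly strong, takes most of the OS scenarios to three months or more. This should be settled before the outcome comparison is run.

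**What to change.** 1. Reconcile Secondary objectives, Study design, Primary endpoints and Progression free survival so that they name one analysis set for each outcome, and state the OS origin.
2. Make the primary OS contrast and the main PFS contrast all reresected GLOW patients versus all reresected historical patients meeting the same eligibility criteria, from the date of reresection, whatever treatment followed. This matches Study design and the Discussion's statement that the study is about a diagnostic strategy and not the treatments. With comparable cohorts, the expected gain under no effect is zero.
3. Restate the three-month target for that contrast. A true three-month gain in roughly 38–51 treated patients moves the whole-cohort median by only about 0.5–0.9 month.
4. Report the WGS-treated subset as secondary only, with the same landmark in both cohorts (alive for OS; alive and progression-free for PFS) or with treatment start as a time-dependent covariate. Say that residual fitness selection remains. Drop the direct treated-versus-historical contrast from reresection.

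**Cost.** The changes are to protocol and SAP wording; the treatment start date is the main extra item needed. The real price is a diluted effect, a less favourable target than three months, and a few early events lost in the landmark analysis.
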